## Methods/Design

### Hypothesis 

We hypothesized that patients receiving LSE with RUSI biofeedback will demonstrate significant improvement in LMM CSA, pain, functional disability, and QOL compared to those receiving LSE without RUSI biofeedback or minimal intervention (control). 

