### Sample size calculations

Considering the minimum detectable change of 1.0 cm or 100 mm reported for LMM CSA [50], the sample size was estimated a priori to detect a minimum difference of 1.0 point  in LMM CSA between LSER and LSE, or 2.0 points between LSER and minimal intervention, assuming a common standard deviation (*SD*) of 2.5 points based on our pilot study [29], a medium effect size of 0.32, an alpha of 0.05, statistical power of 85%, and a correlation of 0.5 among repeated measures,  for between–within repeated measures analysis of variance (ANOVA). The calculations revealed that a sample size of 75 is required. However, while anticipating a 20% dropout rate (*n* = 15), a total sample size of 90 (30 per group) will be finally required. The sample size was calculated using G Power 3.1.9.2 software [51].

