### Data processing and statistical analyses

All data will be carefully recorded in a logbook and electronically using Microsoft Excel sheets. Data values will be double-checked for missing values and errors before transfer into SPSS for reporting and statistical analysis. Intention to treat (ITT) analysis will be applied with all randomized participants who have any outcome data available for analysis, included in the trial regardless of the presence or absence of follow-up. All statistical analyses will be conducted on IBM SPSS Statistics version 23.0 (IBM Co., Armonk, NY, USA) with a *P*-value < 0.05 to be considered significant for all tests.

A normality test for the dependent variables will be examined using the Kol mogorov–Smirnov and Shapiro–Wilk test. Descriptive analysis will be used to summarize the data with the use of mean (SD), frequencies, and percentages. One-way ANOVA (for normally distributed data) or Kruskal–Wallis (for skewed data) test will be used to compare baseline continuous variables whereas the chi-square test will be used to compare baseline categorical variables among the three groups. Mixed between–within subject ANOVA will be applied to evaluate time effect, group effect, and group by time interaction effect  in all outcomes if the data is normally distributed. Otherwise, Friedman’s ANOVA and Kruskal–Wallis test will be applied to evaluate within-group and between-group differences, respectively, when the data is skewed. Post hoc analysis will be applied for any significant within- or between-group differences detected. The effect size will be computed to evaluate the magnitude of change in all the outcomes. To examine the relationship between changes in LMM CSA and pain or disability, correlation and regression analyses will be performed for all the intervention groups.

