## Discussion

Previous small RCT (*n* = 41) suggests that a 4-week LSE training with RUSI biofeedback may improve LMM CSA in patients with non-specific acute LBP compared to analgesics alone [28]. In contrast, in an RCT by Partner and colleagues [31] to compare LMM thickness in patients with NCLBP before and after a single session of LSE with and without biofeedback including the use of RUSI, no significant inter-group difference was detected for LMM thickness. Their study [31] however is underpowered, suffered a small sample size (*n* = 22), and included a single exercise session which may not be adequate to induce a significant change in the outcome observed. Taking into account  methodological limitations of these trials [28, 31], a powered RCT will be conducted to determine  the effectiveness of 8-week LSE training with RUSI biofeedback compared to LSE training without biofeedback, or minimal intervention in individuals with NCLBP. After the intervention, outcomes will be also evaluated at the 3-month follow-up and possibly at the 6-month or 12-month follow-up. If our hypothesis is correct, this study has the potential to inform  the decision to change practice by providing evidence for the clinical effectiveness of LSE with RUSI biofeedback on enhancing recovery of LMM size, which is commonly implicated in LBP and reoccurrence [5]. 

As a secondary objective, the present study will seek to examine the relationship between p ost-treatment change in LMM CSA and pain as well as disability. This may help to establish causality effect regarding LSE training with RUSI biofeedback on LM M morphology (i.e., CSA) and LBP and LBP-related disability.

This study however is without some limitations. The measurement of LMM CSA will be only performed at the L5 level even though aberrations in LMM morphology are commonly observed at this level [30, 41], besides evidence of recovery following specific rehabilitation [28, 30]. Therefore, any changes in the LMM CSA in other levels of the lumbar spine following rehabilitation could not be detected. Furthermore,  other important LMM morphological-related outcomes such as fat infiltration, volume, and percentage thickness will not be evaluated due to limited resources. Nevertheless, the planned powered, single (assessor) blind, three-arm (including comparator and active control groups), parallel RCT design is the strength of our study.  

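### The mixed ANOVA does not say which of its tests answers the primary objective, and the one the trial was sized on averages in baseline, so its power is about 50 to 58%, not 85%

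*Protocol article*

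**What the plan says.** Under Data processing and statistical analyses, the article applies a mixed between-within ANOVA to every outcome "to evaluate time effect, group effect, and group by time interaction effect". The threshold is "0.05 to be considered significant for all tests". The follow-up rule is: "Post hoc analysis will be applied for any significant within- or between-group differences detected". No baseline covariate is named, and none of the three effects is designated as the answer to the primary objective.

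The Hypothesis section sets LSER against LSE and against minimal intervention. Sample size calculations gives target differences of 1.0 and 2.0 points for these two comparisons. They are joined by an 'or' and not ranked. Outcome assessment lists baseline, 8 weeks and 3 months, with no primary visit.

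The sample size rests on "a medium effect size of 0.32, an alpha of 0.05, statistical power of 85" per cent and "a correlation of 0.5 among repeated measures", with an SD of 2.5 points. It gives 75 participants, raised to 90 for dropout.

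**The concern.** The hypothesis concerns two between-arm differences after treatment. The planned tests do not line up with it:

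- The group main effect compares arm means over all measurements. If baseline is one of them, the effect is averaged with a visit at which no difference is expected.
- The group-by-time test is a valid treatment test, but it is an omnibus test on 4 degrees of freedom and is not named as decisive.
- The time effect is not a treatment comparison. If every arm gained the 1.7 points that the Background reports from the pilot study, it would be significant in practically every trial whether or not biofeedback works. It can nevertheless trigger within-group post hoc tests.

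Two things are at stake: whether the trial has the power it claims, and whether the primary conclusion depends on which F test is later put forward.

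**Working it through.** **1. Inputs.** From Sample size calculations: f = 0.32, alpha 0.05, power 85%, r = 0.5, SD 2.5, differences 1.0 and 2.0, N = 75 raised to 90. From Outcome assessment: m = 3 measurements. From the randomisation section: k = 3 equal arms.

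**2. The stated N.** For the group main effect, λ = f²·N·m / (1 + (m − 1)r), with 2 and N − 3 degrees of freedom. At N = 75, λ = 0.1024 × 75 × 3 / 2 = 11.52 and power is 0.854. At N = 72 it is 0.838. So 75 is reproduced exactly. The alternatives do not match:

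| Test | Measurements | N for 85% |
|---|---|---|
| Group main effect | 3 | 75 |
| Group main effect | 2 | 84 |
| Group main effect | 4 | 72 |
| Group-by-time | 3 | 27 |
| Time | 3 | 21 |

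**3. Dilution.** Let the difference be d at both follow-ups and 0 in expectation at baseline. The difference in three-visit means is (0 + d + d)/3 = 2d/3. Then f = 0.32 × 2/3 = 0.213.

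- N = 75: λ = 0.0455 × 75 × 3 / 2 = 5.12, power 0.496.
- N = 90: λ = 6.14, power 0.579.
- N needed for 85%: 165.

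Starting from the target differences gives the same picture. Means of 0, 1 and 2 for control, LSE and LSER have SD 0.8165, so f = 0.8165/2.5 = 0.327. After dilution, power is about 51% at 75 and 60% at 90.

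**4. Group-by-time test.** With those post-treatment means and equal baselines, the interaction deviations are ±(2/3, −1/3, −1/3) in the outer arms and 0 in the middle arm. Their sum of squares is 2 × (4/9 + 1/9 + 1/9) = 4/3. Then λ = n × (4/3) / (2.5² × 0.5).

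- n = 25: λ = 10.67, df 4 and 144, power 0.73.
- n = 30: λ = 12.8, df 4 and 174, power 0.82.

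**5. False positives with no treatment effect.** If a significant group or interaction effect alone were read as success, the rate would be 1 − 0.95² = 9.75% (simulated 9.6 to 9.9%). If a significant omnibus effect is required first, followed by an unadjusted LSER contrast at a follow-up visit, simulation gives about 6%. Allowing any pair of arms gives about 7%.

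**6. Baseline-adjusted contrasts at one visit.** Residual SD = 2.5 × √(1 − 0.5²) = 2.165 and SE = 2.165 × √(2/n), which is 0.612 at 25 per arm and 0.559 at 30. Normal-approximation power is Φ(d/SE − 1.96):

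| Contrast | 25 per arm | 30 per arm | Simulated with t tests |
|---|---|---|---|
| LSER-LSE, 1.0 | 0.37 | 0.43 | about 36% and 42% |
| LSER-control, 2.0 | 0.90 | 0.95 | about 89% and 94% |

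Under Holm the smaller p-value is tested at 0.025 (critical value 2.241). If that is LSER-control, its approximate power falls to Φ(2/0.612 − 2.241) = 0.85 at 25 per arm and Φ(2/0.559 − 2.241) = 0.91 at 30. LSER-LSE loses little, since it is usually tested second, at 0.05.

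**The case against.** The article never says in words that baseline is a level of the time factor. That is an inference from three scheduled measurements, no covariate, and the exact match of N = 75 at m = 3 only. It is a strong inference, and no other variant tried gives 75.

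The group-by-time test is the natural treatment test in this model, and it already uses baseline through within-person change. This stands. The advantage of covariate adjustment over it depends on r: the three-arm omnibus ANCOVA at 8 weeks against the interaction has about 81% against 73% power at r = 0.5, 94% against 93% at r = 0.7, and 99% for both at r = 0.8 (25 per arm). But the article neither designates the interaction nor sized the trial on it.

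A reader might infer that the plan doubles the false-positive rate. The text does not support this. The 9.75% needs a rule that any significant omnibus effect means success, and no such rule is stated. Ungated contrasts would give about 9% (two at one visit) or 16% (two at two visits), but the plan runs post hoc tests only after a significant result. The gated figure of about 6% assumes that no arm differs from another; gating protects less if only one contrast is null. The post hoc method is unstated, and adjusted p-values would also fit a 0.05 threshold. That detail may properly sit in an analysis plan not shown here.

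A reader might also infer that later visits would alter the primary model, since the Discussion says outcomes will be "evaluated at the 3-month follow-up and possibly at the 6-month or 12-month follow-up". The schedule fixes three assessments, and nothing puts later ones in that model.

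**Conclusion.** The point holds as a mismatch between hypothesis, sizing and analysis. The deciding test and visit are not named. The test that yields N = 75 has about 50% power at 75 and 58% at 90 once baseline is recognised as a visit with no expected difference, so the stated 85% is not met for it. The interaction is in better shape at about 73% and 82%, but is not the designated test. Error-rate inflation is modest under the stated gating and is not the main ground for change.

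The figures rest on the plan's own SD of 2.5 and r = 0.5, equal correlation between visits, and a difference that is the same at 8 weeks and 3 months. A higher r lowers the power of the group main effect (the denominator 1 + 2r grows) and raises that of the interaction and the adjusted contrasts.

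**What to change.** Make the primary analysis the baseline-adjusted between-arm difference in multifidus cross-sectional area at one named visit, such as 8 weeks. Use ANCOVA, or a mixed model with baseline as covariate. Report LSER-LSE and LSER-control with 95% confidence intervals and Holm adjustment across the two. Treat the other visit as secondary. State that the group main effect, the time effect and within-group tests are not evidence of effectiveness.

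Restate the power for these two contrasts at the planned size, using the figures above, without enrolling more participants.

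Baseline is already collected, so no new data are needed. There are three costs. Holm lowers power, by about 4 to 6 points for LSER-control in the approximation above and very little for LSER-LSE. The restated power for LSER-LSE, the comparison that isolates biofeedback, is far less favourable than 85%: about 85 per arm would be needed to reach that for 1.0 point. Finally, Trial status expected follow-up to end on 30 September 2021 and dates the current version 4 October 2021. The change therefore needs a dated amendment confirming that it was made before anyone saw outcome data by arm. If that cannot be confirmed, the analysis should be reported as specified after the fact.

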According to the latest systematic review [32] to summarize the evidence regarding the effectiveness of LSE on LMM morphology, very low- to low-quality evidence exists that LSE improves LMM CSA post-intervention or compared to medication, general exercise, or general physiotherapy in patients with non-specific LBP. However, only one RCT [28] (conducted among acute LBP patients) of the five included RCTs [28, 33–36] used RUSI as biofeedback. Furthermore, on the basis of two small trials [28, 37] in which one included patients with acute LBP [28] and the other included patients with  chronic LBP [37], the review [32] found no evidence to support the correlation between changes in LMM CSA  and changes in pain or disability. Thus, it is imperative to explore  if the addition of RUSI biofeedback in LSE training would provide more favorable effect on LMM CSA compared to LSE training without RUSI biofeedback, and to examine the correlation between changes in LMM CSA and LBP or LBP-related disability among individuals with NCLBP. 

Our recent pilot study [29], even though was limited to being a single-group pretest-posttest design, suggests the feasibility of conducting a large-scale RCT  to determine the efficacy of LSE with RUSI biofeedback in individuals with NCLBP. The use of LSE with RUSI biofeedback resulted in significant improvement in LMM CSA by 1.7 points, pain by 3.9 points, and  disability by  4.5 points. However, no significant improvement in  physical and mental health was observed after the intervention, which could be attributed to the shorter treatment (12 sessions) provided [29]. Thus, the purpose of this study is to determine the effectiveness of LSE with RUSI biofeedback in individuals with NCLBP. The primary outcome will be LMM CSA whereas the secondary outcomes include  pain, functional disability, and QOL. 

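### The two hypothesised LSER comparisons depend on a significant three-arm test, so a formal LSER–LSE contrast with its precision may go unreported, and is mildly inflated when it is reported

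*Protocol article*

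**What the plan says.** All of this is in the protocol article.

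- **Hypothesis.** Improvement with LSER is to be shown "compared to those receiving LSE without RUSI biofeedback or minimal intervention (control" group. These are two pairwise comparisons, both against LSER.
- **Background.** The stated need is to find out "if the addition of RUSI biofeedback in LSE training would provide more favorable effect on LMM CSA compared to LSE training without RUSI biofeedback".
- **Sample size calculations.** The trial is sized "to detect a minimum difference of 1.0 point" in muscle cross-sectional area between LSER and LSE, "or 2.0 points between LSER and minimal intervention".
- **Data processing and statistical analyses.** The planned tests are overall ones: "Mixed between–within subject ANOVA will be applied to evaluate time effect, group effect, and group by time interaction effect". If the data are skewed, "Friedman’s ANOVA and Kruskal–Wallis test will be applied to evaluate within-group and between-group differences, respectively, when the data is skewed". Arms are compared in pairs only by the next rule: "Post hoc analysis will be applied for any significant within- or between-group differences detected". Two statements do not depend on significance. One is the descriptive summary by mean (SD). The other reads "The effect size will be computed to evaluate the magnitude of change in all the outcomes".

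**The concern.** The comparisons that the trial was designed to make are handled as unplanned follow-up. The three-arm test also responds to LSE against control, which is not part of the hypothesis, and it can be non-significant while LSER truly exceeds LSE by the target amount. In that case the rule as written calls for no LSER–LSE contrast, and readers would not be shown how large a benefit remains compatible with the data. When the overall test is significant, the trials that report the contrast tend to be those in which it came out large, so the reported value overstates the effect on average.

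This is a conditional rule that the article states, so it is not a matter of detail left to an analysis plan that is not shown.

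**Working it through.** **Inputs from Sample size calculations:** LSER−LSE = 1.0, LSER−control = 2.0, SD 2.5, f = 0.32, alpha 0.05, power 85%, correlation 0.5, 75 evaluable (25 per arm), 90 randomized (30 per arm). There are three visits: baseline, 8 weeks and 3 months.

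**1. The plan's own figure.** The two differences imply arm effects of 0/1/2 for control/LSE/LSER. The SD of these means is √[(1+0+1)/3] = 0.816, so f = 0.816/2.5 = 0.327, in line with the stated 0.32. For the between-group test in repeated-measures ANOVA:

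λ = f²·N·m / [1+(m−1)ρ] = 0.32² × 75 × 3 / (1 + 2 × 0.5) = 11.52, with df 2 and 72.

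Power is 0.854, so the 75 is reproduced. It is the sample size for the overall three-group test, not for LSER against LSE.

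**2. How often the rule blocks the contrast.** I simulated the mixed ANOVA with at least 20,000 trials per scenario, arms equal at baseline, and the same effect at both later visits. Pairwise comparison of arms was allowed if the group or the group-by-time test gave p < 0.05. A significant time effect was taken to open comparisons between visits, not between arms. The true LSER−LSE difference is 1.0 in every row.

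| Effects control/LSE/LSER | r | Per arm | Contrast blocked | Mean LSER−LSE when allowed |
|---|---|---|---|---|
| 0/1/2 (protocol) | 0.5 | 25 | 13% | about 1.06 |
| 0/1/2 (protocol) | 0.5 | 30 | 7% | about 1.03 |
| 0/0.5/1.5 (assumed) | 0.5 | 25 | 36% | about 1.15 |
| 0/0.5/1.5 (assumed) | 0.5 | 30 | 27% | about 1.11 |
| 0/0/1 (assumed) | 0.5 | 25 | 58% | about 1.28 |
| 0/0/1 (assumed) | 0.5 | 30 | 51% | about 1.24 |

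With 0/1/2 and an assumed r = 0.8 (25 per arm), the group-by-time test alone already opens the gate in 99% of trials, with mean estimate 1.00. If LSER equals LSE and both beat control (0/2/2), there is no bias.

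**3. Power for LSER against LSE** (25 per arm, r = 0.5), gated plan against an ungated Holm test of the two hypothesised contrasts:

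- 0/1/2: 27.9% gated, 27.4% Holm, so no loss.
- 0/0.5/1.5: 24.6% gated, 25.2% Holm, a loss of 0.6 points.
- 0/0/1: 19.4% gated, 22.1% Holm, a loss of 2.7 points.

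A single uncorrected test has only about 28.5%, so the low power comes from the sample size and not from the gate.

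**4. What an unconditional estimate would show.** The 95% half-width is 1.96 × 2.5 × √(2/n): 1.39 with 25 per arm and 1.27 with 30. Adjusting for baseline multiplies this by √(1−0.5²) = 0.866, giving 1.20 and 1.10. All four exceed the 1.0-point target, so a null overall test would often leave a 1.0-point benefit neither shown nor excluded. Only an interval makes that visible.

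**The case against.** The strongest reply has four parts.

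- **Testing pairs after an overall test is a standard way to limit multiplicity across three arms.** This stands for significance claims, and the power comparison bears it out. It is no reason to make estimation conditional as well.
- **A reader might infer that the LSER–LSE effect would never be estimated.** The document does not support that. Means and SDs are planned without condition, and from these and the group sizes a crude difference and interval can be worked out at each visit. The effect-size sentence is also unconditional, and does not say whether it means change within an arm or a difference between arms. What remains is that neither statement commits to an LSER–LSE contrast, and visit-wise SDs do not give the precision of a change-score or baseline-adjusted difference.
- **Much larger figures can be produced.** With 0/0/1, r = 0.5, 25 per arm and only the group-by-time test as gate, the contrast is blocked in 72% of trials, the mean estimate is about 1.53, and power falls from 28.5% to 17%. But the article plans both group and group-by-time tests, its own figures imply 0/1/2, and the power comparison is with an uncorrected test. These figures should not be used as the headline.
- **An article may leave confidence intervals and the definition of contrasts to a fuller document.** That is accepted for their absence. The point here is the conditional rule, which is stated.

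That a null result would be read as no benefit is speculation about reporting, and the conclusion does not rest on it.

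**Conclusion.** The point holds in a limited form. The analysis section makes the two hypothesised comparisons post hoc and conditional. Under the protocol's own assumptions the consequence is modest: no formal contrast in 7% to 13% of trials, and an average overstatement of about 3% to 6%. It becomes serious if LSE adds little over minimal intervention: 51% to 58% blocked and 24% to 28% overstatement under 0/0/1. That pattern is an assumption, but not a remote one. Under Interventions, both exercise groups also perform the control exercises, and the Background grants that LSE may not be superior to other exercise programs.

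The gain from changing the rule lies in unconditional and less biased estimation, not in power. The sizes rest on SD 2.5, r = 0.5, equal baselines, equal effects at both follow-ups, and the reading that either the group or the group-by-time test opens the gate.

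**What to change.** Replace the post hoc sentence with, for example: *LSER minus LSE and LSER minus minimal intervention will be estimated for every outcome, whatever the overall test shows, and reported as mean differences in original units with 95% confidence intervals. For significance claims on the primary outcome, Holm's procedure will be applied across these two contrasts. Post hoc testing is kept for LSE versus minimal intervention.* Tie the effect-size sentence to the same between-arm differences.

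The cost is two sentences, with no new participants, visits or measurements, so the change is still possible at the analysis stage even if follow-up has ended as the Trial status section expects. The downside is that two contrasts are tested directly, which is why a simple multiplicity step is needed. The change will not cure the low power for a 1.0-point difference, but the interval will show it openly.
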